### Data collection

Data is collected from clinical proformas, clinical notes and study-specific forms and then entered onto an online data and management system (MACRO by InferMed (https://www.elsevier.com/solutions/macro)). The database has been programmed by KCTU and is hosted on a dedicated secure server within Kings College London. No identifiable data will be entered on the database. Participants will be identified using a unique code and initials.

### Trial Steering Committee

The Trial Steering Committee (TSC) will include an independent chair, two independent members, an independent patient representative and at least one study statistician. The committee will meet with the research team bi-annually to monitor and supervise the progress of the trial, accumulating safety data and other sources of relevant information.

### Sample size and recruitment

The main aim of the study is to identify a suitable way to measure necrosis and estimate the event rate in each arm. We also aim to estimate recruitment and retention rates and explore the potential impact on the outcome by stratification factors. In order to do this with sufficient precision to inform the design of a later definitive study, the sample size calculations have been based on estimating with precision and not hypothesis testing.

The study will take place at Guy’s and St Thomas’ NHS Foundation Trust (GSTT) in the department of plastic surgery. Within GSTT over 150 SSMs are performed per year and recruitment will occur for 2 years. Three hundred participants would allow us to estimate the 95% confidence intervals (CIs) for the recruitment rate with precision of at least ± 6 percentage points (calculation based on proportion requiring the largest sample size, e.g. 50%). Based on our previous experience, we anticipate that the actual recruitment rate will be no less than 60% so this would provide us with at least 180 participants. Assuming the proportion of necrosis events among participants in the control arm is 30%, this number will allow us to estimate ‘necrosis’ rates to within each arm to at least ± 9 percentage points. If the true difference between event rates were 15%, we will be able to estimate this within ± 12 percentage points.

We anticipate that the four consultant plastic surgeons will perform at least 30 operations each during this period (approximately 15 per arm). This sample size will also allow us to estimate means and 95% CIs for secondary outcomes and will provide an adequate number of participants in subsets (smokers, diabetics and radiotherapy patients) in order to be able to estimate the standard deviation for the continuous outcomes.

Patients will be recruited from the outpatient clinic ideally at their first appointment with the surgical team at GSTT. The second point of recruitment will be at a patient’s pre-assessment clinic if they have not been asked at their initial appointment.

### Statistical methods

#### Analysis principles

The analysis will be conducted in accordance with a pre-defined statistician analysis plan, which is described in detail below. As this is a feasibility study, the analysis for this trial will be primarily descriptive. Summary statistics will be calculated to assess feasibility aims such as the measurement of necrosis, recruitment and retention rates, surgical versus conservative management of skin necrosis and acceptability measures for patients.

Data will be analysed on an intention-to-treat (ITT) principle (i.e. all participants with a recorded outcome will be included in the analysis and will be analysed according to the treatment group to which they were randomised.) No imputation for missing data will be performed. The proportion of missing data for each outcome will be reported. Confidence intervals (CI) will be 2-sided and at the 95% level. All data will be analysed using Stata/IC (StataCorp, College Station. TX, USA).

### Analysis plan

#### Baseline comparability of randomised groups and flow of patients

A Consolidated Standards of Reporting Trials (CONSORT) Extension to Pilot and Feasibility Trials checklist flow chart will be constructed [15, 16]. This will include the number of patients screened, number of eligible patients, number of patients randomised, number of patients withdrawing and lost to follow-up, the number continuing through the trial and the number included in the analyses. Baseline characteristics listed in Table 2 will be summarised by treatment group using suitable measures of central tendencies (mean and median) and variability (standard deviation—SD and interquartile range—IQR) for continuous data, and frequencies and proportions for categorical data. No significance testing will be undertaken.

**Table 2 Tab2:** Baseline/pre-operative/operative/post-operative variables

Baseline variables:
Age (years), ethnicity, height, weight, diabetic, hypertensive, smoker, smoking history, BRCA carrier, neoadjuvant therapy, previous breast surgery on study breast, type of previous breast surgery, oncological reason for mastectomy, prophylactic reason for mastectomy.
Pre-operative variables:
Pre-operative variables: measurement notch to nipple, inframammary fold to nipple, breast cup size, sensory changes, sensory changes due to, degree of breast ptosis, type of reconstruction (implant/autologous based) study breast.
Operative variables:
Surgery (yes/no), reason for no surgery if no, breast surgeon, plastic surgeon, side of study breast, type of construction, type of mastectomy, surgical technique for mastectomy, infiltration used, type of breast reconstruction, axillary clearance, core temperature pre first incision, environmental temperature pre first incision, mastectomy skin flap thickness (for upper outer, lower outer, lower inner, upper inner quadrants), mastectomy skin flap thickness measurement method, mastectomy breast weight, reconstruction flap weight, implant/expander volume, type of implant used, core temperature post reconstruction, environmental temperature post reconstruction, number of drains, duration of operation, intra-operative complications.
Additional post-operative outcomes:
Wound infection additional antibiotic course, type of antibiotic given, post-operative seroma, seroma required draining, site drainage of the seroma performed, method to detect seroma, post-operative haematoma required surgery, surgical intervention for complications of reconstruction, surgical re-intervention for reconstruction complication, repeated surgical interventions.

#### Pre-operative and operative characteristics by randomised group

Pre-operative and operative variables listed in Table 2 will be summarised by treatment group using suitable measures of central tendencies and variability for continuous data and frequencies and proportions for categorical data. No significance testing will be undertaken.

#### Analysis of primary outcome

As the anticipated number of events (necrosis yes/no) is expected to be relatively few (approximately 40 events in total: 30% control; 15% in intervention), the unadjusted proportion of participants with skin necrosis within 30 days in each trial arm with corresponding 95% CI will initially be calculated. Results will then be tabulated by treatment group for minimisation variables, smoking (yes/no), diabetic (yes/no), autologous- or implant-based reconstruction (yes/no), BRCA carrier status (yes/no).

For necrosis depth (SKIN score), we will present the unadjusted proportions of patients within each category by treatment arm, as assessed by the primary clinical assessor at time of first occurrence (or assessment if none throughout). For patients with necrosis, we will present measures of central tendencies (mean and median) and variability (standard deviation (SD) and interquartile range (IQR)) for necrosis area (3), measured in mm^2^, by treatment arm as assessed by the primary clinical assessor at time of first occurrence. Area will be reported overall (sum of areas by depth) and separately by depth grading.

Necrosis depth (SKIN score) and area measurements will be plotted over time for each individual by treatment group. We will examine the area assessments over time with a view to considering the area under the curve (AUC) as an additional summary estimate. For each patient, we will also determine the maximum depth and area as assessed by the primary assessor over the follow-up period and present the unadjusted proportions of patients within each category. For maximum necrosis area, we will present mean, median, SD and IQR by treatment arm. The proportion of patients for whom the necrosis has been resolved/fully healed within the 30 days will be presented by treatment arm with 95% CI.

The agreement between the primary and secondary assessors clinical assessment of necrosis presence (yes/no) and depth (SKIN score) will be assessed using Fleiss’ kappa statistic, κ [17]. For each patient who experiences necrosis, we will include the first occasion where necrosis has been indicated by at least one of the two assessors, i.e. at the time of first appearance. For patients who do not experience necrosis during the follow-up period, we will include the first occasion where both assessors rate the depth as none. Fleiss’ kappa statistic is appropriate since each patient is rated by the same number of assessors (*n* = 2), but the assessors are not necessarily the same over all patients. Kappa values can vary from − 1 (complete disagreement) through 0 (chance agreement) to + 1 (complete agreement). Intermediate kappa values will be interpreted using the criteria described by Landis and Koch [18] where κ < 0 = poor agreement, 0 < κ ≤ 0.20 = slight agreement, 0.20 < κ ≤ 0.40 = fair agreement, 0.40 < κ ≤ 0.60 = moderate agreement, 0.60 < κ ≤ 0.80 = substantial agreement and 0.80 < κ < 1 = almost perfect agreement.

The presence (yes/no) and depth (SKIN score) agreement for necrosis will be assessed using Fleiss’ kappa statistic between the two photographic assessors, the primary clinical assessor and photographic assessor 1 and the primary clinical assessor and photographic assessor 2.

The agreement between the first and second assessors clinical assessment of total necrosis area will be assessed using the method of Bland and Altman [19]. That is, we will visually inspect a plot of the difference between the two assessors for each assessment measuring the same quantity, i.e. for the same patient and same time, against their mean and present 95% limits of agreement calculated as d ± 1.96 s, where d denotes the mean difference and s denotes the standard deviation of the differences. The limits of agreement represent the region in which 95% of differences will lie (assuming normality of differences).

The degree of absolute agreement among area measurements will also be measured using an intraclass correlation coefficient (ICC). This will be estimated from a one-way random effects ANOVA model as different assessors are used across patients, i.e. the two assessments do not differ in a consistent way [20]. For the recorded area (in mm^2^) for patient *i* assessed by assessor *j*, denoted as *y*_*ij*_ the model to be fitted therefore will be the following:$$ {y}_{ij}={\beta}_0+{r}_i+{w}_{ij} $$for, *i* = 1,…,*n* patients, *j* = 1,…,2 assessors, *β*_0_: overall mean of the assessor ratings, $$ {r}_i\sim N\left(0,{\sigma}_r^2\right), $$ and $$ {w}_{ij}\sim N\left(0,{\sigma}_w^2\right). $$
$$ {\sigma}_r^2 $$ is the variability across patients and $$ {\sigma}_w^2 $$ is the unexplained variability across the assessments for the same patient. The ICC which represents the extent to which there is absolute agreement among the assessors is estimated as$$ \mathrm{ICC}=\frac{\sigma_r^2}{\sigma_r^2+{\sigma}_w^2}. $$

The ICC ranges from 0 to 1; if the unexplained measurement variability across the assessors for the same patient is small in comparison to the true variability across the patients, the ICC will be close to 1. We will also asses the agreement in area between the first and second assessor separately by depth grading where data allows using the outlined methods.

To enable the comparison of the three different necrosis outcome measures, we will categorise necrosis area measurements (agree/do not agree) for all patients if they are within ± 2.5% (total error margin of 5%) calculated agreement between assessors using Fleiss’ kappa statistic.

All this information will be assessed by the Trial Steering Committee to determine the most suitable and discriminating way in which to measure necrosis. To aid the decision process, a performance matrix [21] will be constructed (see Table 3). The performance of each measurement method against three key specified criterion will be completed.

**Table 3 Tab3:** Performance matrix

Criteria	Outcome measure		
	Necrosis Y/N	Depth (SKIN)	Total necrosis area
Subjectivity of measurement (κ for the first and second clinical assessment)*			
Sample size required to demonstrate statistically significant difference between treatment and control arm (based on observed data)^†^			
Proportion of patients with observed response**			

*For total necrosis area, we include κ where area is assumed to be 0 mm^2^ when no necrosis present is recorded. ^†^For necrosis Y/N sample size will be determined for a two sample proportions test. For total area, sample size will be computed using non-parametric methods for non-normally distributed continuous data [22]. For necrosis depth sample size calculation for ordered categorical data will be performed using the observed proportions in each category [23]. **For total necrosis area, we will present the proportion of patients with an observed area response where area is assumed to be 0 mm^2^ where no necrosis present is recorded

The performance of each method of measurement will then be compared pairwise against all the others for each criterion. For each pairwise comparison, the superior method will be assigned a score of 1 for the associated criteria. Superiority will be declared for a higher κ statistic, lower sample size and higher proportion of patients with observed response. For ties (equal performance), we will assign each measurement a score of ½. For each pairwise measurement comparison, a total superiority score will be computed for each measurement by summing the number of criteria the measurement is superior for. The total number of criteria each measurement is superior for, summed over comparisons with each other measurement methods, will be computed to establish an overall priority performance ranking. This ranking can be used by the TSC to facilitate the decision process; however, it is not obligatory or necessarily prescriptive. Additional qualitative feedback from clinicians and patients on acceptability of measurement use will also be important to consider.

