### Randomisation and blinding

Participants will be allocated to treatment arm via an online randomisation system hosted by the King’s College London Clinical Trials Unit (KCTU) to ensure concealment of treatment allocation for clinicians who are assessing participants. Randomisation is undertaken with equal allocation to each arm (1:1) using minimisation stratifying for the following:Type of reconstruction (Implant vs Autologous)Smoking status (yes/no)Diabetic (yes/no)BRCA carrier status (yes/no)

Surgeons and outcome assessors will be blind to treatment allocation.

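### The all-patient depth (SKIN) kappa mostly re-measures agreement on presence, so grading with no reliability would still score about 0.5 to 0.7; a kappa restricted to graded necrosis should sit beside it

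*Protocol article*

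**What the plan says.** All references are to the Protocol article.

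- **Statistic.** Under Analysis of primary outcome, agreement between the two clinical assessors on "necrosis presence (yes/no) and depth (SKIN score) will be assessed using Fleiss’ kappa statistic". The same statistic is planned for the photographic comparisons.
- **Which assessment is used.** One rule serves both presence and depth. For a patient with necrosis, "we will include the first occasion where necrosis has been indicated by at least one of the two assessors". For a patient without, "we will include the first occasion where both assessors rate the depth as none".
- **Scale.** The Primary outcome section defines SKIN as four levels. A means no necrosis; B, C and D are increasing grades.
- **Interpretation.** Kappa is read in labelled bands, including "0.60 < κ ≤ 0.80 = substantial agreement". The band from above 0.40 up to and including 0.60 is moderate.
- **Use.** Row 1 of Table 3 is "Subjectivity of measurement (κ for the first and second clinical assessment"). The text after the table counts a higher kappa as superior in each pairwise comparison.
- **Expected events.** "approximately 40 events in total: 30% control; 15% in intervention".

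Area agreement is also to be examined separately by depth grade where data allow. No depth kappa restricted to patients with necrosis is described.

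**The concern.** SKIN depth is presence (A versus the rest) plus a grade (B, C or D). Only the grade is new, because presence has its own kappa. When most patients are rated A by both assessors, a single four-category kappa is dominated by the presence part and says little about whether two assessors give a necrotic area the same grade.

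Choosing how to measure necrosis is half of the trial's primary objective. The Trial Steering Committee will see a depth kappa with a verbal label and a place in the matrix. If that figure can look respectable when grading carries no information, the committee lacks the one reliability figure that bears on what depth adds to yes/no.

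**Working it through.** **Inputs from the document**
- Participants: "so this would provide us with at least 180 participants" (Sample size and recruitment).
- Allocation: "Randomisation is undertaken with equal allocation to each arm (1:1"), so 90 per arm.
- Necrosis rates: 30% control, 15% intervention.

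**Assumptions, not in the document**
- Clinical necrosis yes/no corresponds to SKIN B to D versus A.
- The mix of B/C/D among necrotic cases is varied from equal thirds to 70/20/10.
- Presence disagreement: of the patients flagged by at least one assessor, a share d is flagged by only one, with d from 0 to 0.30.

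**Step 1: reproduce the plan's event count.** 90 × 0.30 + 90 × 0.15 = 40.5, matching the stated figure of about 40. Prevalence p = 40.5/180 = 0.225, so the none/none share is 0.775.

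**Step 2: random grading with perfect agreement on presence.** Kappa = (Po − Pe)/(1 − Pe), with pooled marginals. Let q be the sum of squared B/C/D proportions among necrotic cases. Then Po = (1 − p) + p·q and Pe = (1 − p)² + p²·q.

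Equal thirds (q = 1/3):
- Po = 0.775 + 0.225/3 = 0.850
- Pe = 0.775² + 3 × 0.075² = 0.6175
- kappa = 0.2325/0.3825 = 0.608

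Other mixes at the same prevalence: 50/30/20 gives 0.633, 60/30/10 gives 0.677, 70/20/10 gives 0.722. Equal thirds is the lowest case. Among necrotic cases alone, kappa is 0 by construction.

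**Step 3: what drives the coefficient.** With equal thirds, expected disagreement is 1 − Pe = 0.3825. The none-versus-any part is 2 × 0.225 × 0.775 = 0.34875; the within-grade part is 0.225² × 2/3 = 0.03375. The first is 0.34875/0.3825 = 91%.

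**Step 4: sensitivity to prevalence** (equal thirds, perfect presence agreement). 15% gives 0.630, 25% gives 0.600, 30% gives 0.583, 40% gives 0.545.

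**Step 5: sensitivity to presence disagreement** (p = 0.225, random grading).

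| d (patients of about 40) | Presence kappa | Equal thirds | 50/30/20 | 60/30/10 |
|---|---|---|---|---|
| 0 | 1.00 | 0.608 | 0.633 | 0.677 |
| 0.05 (2) | 0.97 | 0.590 | 0.614 | 0.656 |
| 0.10 (4) | 0.93 | 0.570 | 0.594 | 0.635 |
| 0.20 (8) | 0.86 | 0.529 | 0.551 | 0.588 |
| 0.30 (12) | 0.78 | 0.483 | 0.503 | 0.536 |

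Worked example, d = 0.10, equal thirds: Po = 0.775 + 0.225 × 0.90/3 = 0.8425. The A marginal is 0.775 + 0.01125 = 0.78625. Pe = 0.78625² + 0.21375²/3 = 0.6334. Kappa = 0.2091/0.3666 = 0.570.

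**Step 6: the label in a single trial.** In 5,000 simulated samples of 180 per scenario, random grading exceeded 0.60 in 54%, 76% and 95% of samples (equal thirds, 50/30/20, 60/30/10) at d = 0. At d = 0.20 the figures were 9%, 17% and 39%.

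**Step 7: precision of a restricted kappa.** At n = 40 and kappa 0.6 the simulated standard deviation is 0.107, so the half-width is 1.96 × 0.107 = 0.21. Patients 1 to 34 were graded on the earlier depth categories. Without them, 146 × 0.225 ≈ 33 patients remain, and scaling by √(40/33) gives about 0.23.

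**The case against.** **The all-patient kappa is a legitimate target.** If depth became the definitive outcome, it would be the four-level score on every randomised patient, and its reliability includes A versus B to D. Table 3 keeps a common denominator on purpose, setting area to 0 mm² where there is no necrosis. This stands. It is a reason to keep the all-patient kappa, but it does not supply the missing information on grading.

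**The committee will see the gap.** The presence kappa is reported alongside, and in every scenario above random grading leaves depth well below presence, for example 0.53 to 0.59 against 0.86. The matrix uses the order of kappas, not their labels, and the ranking is not binding. This also largely stands: depth would lose the kappa criterion to yes/no, and no changed ranking is shown here, including against area. But a gap between the two kappas does not tell the reader that grading agreement is zero without a further calculation like the one above.

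**The 77.5% is not given for SKIN.** The 30% and 15% are clinical yes/no rates. SKIN B is colour change suggesting impaired perfusion, and some B grades may not be called necrosis. The A share would then be smaller and the inflation less: 0.545 at 40% non-A with equal thirds. This stands as a stated assumption.

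**A reader might infer that random grading would be labelled substantial.** The document does not support that as a general statement. With equal grades and perfect presence agreement, kappa at 25% necrosis is exactly 0.600, which the plan labels moderate. About 2 presence disagreements in 40 lower the equal-grades case to 0.590, and at a presence kappa of 0.86 all three mixes in the table are moderate. Random here also means random among B, C and D only; assessors who were random on presence as well would score 0.

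**Conclusion.** The point holds in limited form. The planned depth kappa is driven mainly by agreement on presence, and none of the stated statistics isolates agreement on grade. With good agreement on presence and no agreement on grade, it would still come out at about 0.5 to 0.7, labelled moderate to substantial. The upper label needs near-perfect presence agreement or unevenly spread grades. The harm lies in a figure that conceals grading reliability; it is not shown that depth would win the ranking or that a wrong measure would be chosen. The size rests on the plan's event rates, on clinical yes/no matching SKIN B to D versus A, and on assumed grade mixes and presence disagreement.

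**What to change.** In Analysis of primary outcome:

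1. Keep the all-patient depth kappa for comparability across the columns of Table 3.
2. Add a supplementary depth kappa with 95% CI, restricted to assessments where both assessors record B, C or D. Do the same for the photograph-to-photograph and clinical-to-photograph comparisons.
3. Show the restricted value beside the all-patient value in the Depth cell of Table 3, row 1, and state that the Trial Steering Committee reads both when judging depth reliability.

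The cost is a sentence of text and a few lines of code, with no new data. The downside is precision. At most about 40 patients contribute, or about 33 if patients 1 to 34 are excluded, and fewer where assessors disagree on presence. An interval of ±0.21 or wider spans more than one label band, so the restricted kappa can separate 0.6 from 0 but cannot carry the interpretation alone.

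### The area kappa in row 1 of the performance matrix is not a valid kappa: the ±2.5% label belongs to the pair of assessors, so area's place depends on an unstated coding

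*Protocol article*

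**What the plan says.** All references are to the protocol article, Analysis of primary outcome, with Table 3 and its footnotes.

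- **Presence and depth.** "The agreement between the primary and secondary assessors clinical assessment of necrosis presence (yes/no) and depth (SKIN score) will be assessed using" Fleiss' kappa. No weights are named. The stated reason for this statistic is that "each patient is rated by the same number of assessors" (two), although the individuals may differ between patients.
- **Area, as a measurement.** Bland-Altman limits of agreement and an ICC from a one-way random effects model are planned.
- **Area, for the comparison of measures.** "we will categorise necrosis area measurements (agree/do not agree) for all patients if they are within" ±2.5%, described as a 5% total error margin, with "calculated agreement between assessors using Fleiss’ kappa statistic". The Table 3 footnote sets area to 0 mm² where no necrosis is recorded.
- **Use.** Row 1 of Table 3 holds one kappa per measure, first against second clinical assessor. In each pairwise comparison the higher kappa takes 1 point, and ties take ½ each. Rows 2 and 3 cover required sample size and the proportion with an observed response. For row 2, "For necrosis depth sample size calculation for ordered categorical data will be performed using the observed proportions in each category". The Trial Steering Committee is not bound by the resulting ranking.

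**The concern.** Kappa compares observed agreement with the agreement expected by chance from the categories that the assessors assign. For yes/no and depth, each assessor assigns a category. For area, the rule yields one label per pair, so there is no second rating and no chance-expected agreement. To fill the cell, the analyst must invent a coding, and the choice can put area first or last in row 1 on the same data.

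The depth entry has a lesser problem. The plan uses the order of SKIN A to D when it sizes a future trial (row 2) but ignores it when it measures agreement (row 1). There, an A/B disagreement counts the same as an A/D disagreement.

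Choosing the necrosis measure is the trial's primary objective. The matrix is the pre-specified aid to that choice, and the article gives transparency as a purpose of publishing the plan. A cell whose value rests on a coding decided after the data are seen works against that purpose.

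**Working it through.** **Inputs from the article.** About 180 patients, 1:1; necrosis 30% control and 15% intervention; two assessors. Check of the plan's own figure: 90 × 0.30 + 90 × 0.15 = 40.5 events, against the stated figure of about 40. The article gives no kappa, so what follows is illustrative: 180 patients, 40 with necrosis. Measurement error, spread of area and disagreement counts are assumptions.

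**Area kappa under four codings** (a = share of pairs labelled agree)

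1. *One label per pair.* No second rating, so kappa is undefined.
2. *Agreeing pair coded (agree, agree), any other pair (agree, not agree).* Po = a. The pooled margins are (1+a)/2 and (1−a)/2, so Pe = (1+a²)/2 and kappa = −(1−a)/(1+a). This is −0.127 at a = 0.775, −0.053 at 0.90, −0.005 at 0.99, and 0/0 at a = 1. It is never positive.
3. *Each assessor judged against the pair mean.* Both lie equally far from the mean, so both always get the same label. Kappa is 1, or 0/0 if every pair gets the same label.
4. *Readings matched within tolerance share a category, and 0 is a category.* Suppose there is no disagreement on presence. With no matched necroses, Po = 140/180 = 0.778, Pe = (280/360)² + 80 × (1/360)² = 0.606, and kappa = (0.778 − 0.606)/(1 − 0.606) = 0.44. With 6, 11, 20 or 40 of the 40 matched, kappa is 0.52, 0.59, 0.72 or 1.0. The yes/no kappa is 1.0 throughout. If 8 of the 40 pairs disagree on presence, yes/no is 0.861, and area is 0.629 with half of the other 32 matched and 0.876 with all of them matched.

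**How often two tracings would match.** With a per-assessor coefficient of variation CV, the difference has SD CV × √2, and P(match) = 2Φ(tolerance/(CV√2)) − 1.

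| Assumed CV | Difference under 2.5% | Difference under 5% (each within 2.5% of the mean) |
|---|---|---|
| 5% | 28% | 52% |
| 10% | 14% | 28% |
| 20% | 7% | 14% |

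The text fits either column, and the choice changes the match rate by nearly a factor of two.

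**The planned ICC on the same kind of data.** Simulation with a log-SD of 0.8 between patients, zeros included and no disagreement on presence: ICC on mm² is 0.997, 0.988 and 0.956 at CVs of 5%, 10% and 20%. Under coding 2, with the 2.5% tolerance, the kappa is −0.087, −0.106 and −0.115.

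**Which ICC.** With 6 presence-discordant pairs (median 500 mm², log-SD 1), moving from CV 10% to CV 50% changes the ICC on mm² from about 0.89 to 0.70. The ICC on log(1+area) moves only from 0.899 to 0.892, beside a yes/no kappa of 0.898. On the log scale with zeros, the coefficient nearly repeats yes/no agreement.

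**Depth against yes/no** (kappa, pooled margins, illustrative pairs)

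| Disagreements | Yes/no | Depth unweighted | Linear | Quadratic |
|---|---|---|---|---|
| 6 A/B, 4 B/C, 3 C/D | 0.898 | 0.796 | 0.887 | 0.948 |
| 8 A/B | 0.861 | 0.872 | 0.931 | 0.968 |
| 6 B/C, 6 C/D | 1.000 | 0.824 | 0.905 | 0.956 |
| 8 A/D | 0.861 | 0.872 | 0.812 | 0.763 |

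Unweighted kappa is 0.872 whether the 8 disagreements are A/B or A/D. In the first line the order against yes/no reverses with quadratic weights but not with linear ones.

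**The case against.** A reader might infer that area is bound to lose row 1, or that the whole row is settled before any data. The documents do not support that. The never-positive result belongs to one coding, which the article does not state. Coding 3 gives 1, and coding 4 gives a positive value that varies with the data. What stands is that the coding is unspecified and matters.

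A reader might also infer that unweighted kappa condemns depth to rank below yes/no. It does not: depth is ahead when the disagreements are all A/B (0.872 against 0.861). Weighting lowers kappa for A/D disagreements, and the choice of weights is a judgement. The article also has a sound reason for Fleiss' kappa, since assessors differ between patients. The inconsistency between rows 1 and 2 remains, but as a refinement.

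Nor do the documents show that ±2.5% is unattainable; the match rates rest on assumed CVs. Some loss of raw agreement for a finer measure is also to be expected, and row 2 may repay it.

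Finally, the consequences are limited. The committee sees the Bland-Altman limits, the ICC and acceptability feedback, and need not follow the ranking. This lowers the severity but does not supply the missing definition. The article presents itself as containing the detailed analysis plan, so the rule cannot be excused as a detail left to another document.

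**Conclusion.** The row 1 entry for area cannot be computed as written. Its value can be undefined, at most 0, positive but usually below yes/no, or exactly 1, according to a coding and a percentage base that the plan does not give. That result is algebraic and needs no assumption about the data. The match rates, ICCs and depth examples rest on the assumed CVs, area spread and disagreement patterns shown above.

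The depth point is secondary: ignoring the order of the SKIN grades can change its order against yes/no, but whether it does depends on the data and the weights.

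Severity is moderate. Each measure can earn at most 6 points (2 comparisons × 3 criteria). Row 1 supplies 2 of them, and the ranking is advisory.

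**What to change.** Before database lock, amend the row 1 definition as follows.

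- **Area.** Remove the ±2.5% kappa. Enter the planned one-way ICC on mm² with zeros included, as the Table 3 footnote already sets. Show it also among patients rated as having necrosis by both assessors, so that area error is visible. Do not use log(1+area) or ranks with zeros.
- **Depth.** Use a weighted kappa with the weights stated in advance and the unweighted value beside it. With pooled margins, quadratic weights correspond to the one-way ICC, which brings depth and area onto a similar footing.
- **Yes/no.** Keep Fleiss' kappa.
- **±2.5% agreement.** Report it only as a percentage among necroses, with the base stated.

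The cost is plan wording and a few lines of code; no new data are needed. There are two downsides: the depth weights have to be chosen and defended, and the ICC on mm² is sensitive to a few large areas in a skewed distribution.
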